# Effectiveness of a telehealth physiotherapist-delivered intensive dietary weight loss program combined with exercise in people with knee osteoarthritis and overweight or obesity: study protocol for the POWER randomized controlled trial

**DOI:** 10.1186/s12891-022-05685-z

**Published:** 2022-07-30

**Keywords:** Osteoarthritis, OA, Knee, Telehealth, Overweight, Obesity, Weight management, Physiotherapy, Ketogenic diet, Exercise, Physical activity, Clinical trial, RCT

## Abstract

**Background:**

Obesity is associated with knee osteoarthritis (OA). Weight loss, alongside exercise, is a recommended treatment for individuals with knee OA and overweight/obesity. However, many patients cannot access weight loss specialists such as dietitians. Innovative care models expanding roles of other clinicians may increase access to weight loss support for people with knee OA. Physiotherapists may be well placed to deliver such support. This two-group parallel, superiority randomized controlled trial aims to compare a physiotherapist-delivered diet and exercise program to an exercise program alone, over 6 months. The primary hypothesis is that the physiotherapist-delivered diet plus exercise program will lead to greater weight loss than the exercise program.

**Methods:**

88 participants with painful knee OA and body mass index (BMI) > 27 kg/m^2^ will be recruited from the community. Following baseline assessment, participants will be randomised to either exercise alone or diet plus exercise groups. Participants in the exercise group will have 6 consultations (20–30 min) via videoconference with a physiotherapist over 6 months for a strengthening exercise program, physical activity plan and educational/exercise resources. Participants in the diet plus exercise group will have 6 consultations (50–75 min) via videoconference with a physiotherapist prescribing a ketogenic very low-calorie diet with meal replacements and educational resources to support weight loss and healthy eating, plus the intervention of the exercise only group. Outcomes are measured at baseline and 6 months. The primary outcome is percentage change in body weight measured by a blinded assessor. Secondary outcomes include self-reported knee pain, physical function, global change in knee problems, quality of life, physical activity levels, and internalised weight stigma, as well as BMI, waist circumference, waist-to-hip ratio, physical performance measures and quadriceps strength, measured by a blinded assessor. Additional measures include adherence, adverse events, fidelity and process measures.

**Discussion:**

This trial will determine whether a physiotherapist-delivered diet plus exercise program is more effective for weight loss than an exercise only program. Findings will inform the development and implementation of innovative health service models addressing weight management and exercise for patients with knee OA and overweight/obesity.

**Trial registration:**

NIH US National Library of Medicine, Clinicaltrials.gov NCT04733053 (Feb 1 2021).

## Background

The prevalence and burden of obesity is escalating worldwide [1]. Obesity is linked to many health conditions [2], including osteoarthritis (OA), a leading cause of chronic pain and disability [3] and affecting one in five Australians over the age of 45 years [4]. Overweight and obesity is a significant risk factor for the development [5] and progression [6] of knee OA and is associated with an increased likelihood of knee joint replacement surgery [7]. Evidence shows that losing at least 5–10% of body weight provides clinically important improvements in knee pain and function [8–10] and reduces the likelihood of knee joint replacement [11, 12], with greater benefits when dietary weight loss is combined with exercise [8, 13]. Thus, clinical guidelines for knee OA consistently recommend weight loss for those who have overweight or obesity, together with exercise, as a core treatment [14, 15]. However, many patients do not receive any weight loss support from healthcare practitioners [16–18] and there are currently insufficient numbers of, and referrals to, practitioners with specialist weight loss skills, such as dietitians [16]. Innovative models of care that expand practice roles of other healthcare practitioners [19] may help increase access to effective weight loss support for people with knee OA and address this unmet clinical need.

Physiotherapists are primary care providers of therapeutic exercise for people with knee OA and are thus well placed to play a greater role in weight loss support [20]. From a workforce capacity perspective, there are many more practicing physiotherapists than dietitians. For example in Australia, physiotherapists outnumber dietitians in the community by over 4:1 [21, 22]. As exercise and rehabilitation specialists who already manage people with knee OA and often develop strong patient rapport [23, 24], there is opportunity for physiotherapists to integrate and support exercise and dietary weight loss together for synergistic benefit [8, 13]. This also obviates the need for patients to consult multiple practitioners for these treatments which may not be possible due to availability, proximity and cost and which can be time-consuming and less convenient. Physiotherapists also have the advantage of having relatively longer consultation times and often more frequent patient follow-up than other healthcare practitioners, such as family doctors, which may allow greater opportunity for weight loss [20]. Furthermore, the physiotherapy profession has previously demonstrated flexibility in adapting to changes in other health care models beyond their traditional scope of practice, such as by providing psychologically-informed care for complex pain [25].

To play a greater role in weight management over and above simply providing advice about the role of weight in OA, physiotherapists require upskilling as many currently lack the requisite knowledge, skills and confidence to prescribe and support a dietary weight loss intervention [26, 27]. We have shown that a customized self-directed, relatively short (< 10 hours) e-learning program for physiotherapists can substantially increase their confidence in both their knowledge and clinical skills in weight management for patients with knee OA [28]. However, further research is needed to determine whether physiotherapists can use this new knowledge to effectively and safely deliver a dietary weight loss intervention, in addition to other core OA treatments of education and exercise that are within traditional scope of physiotherapy practice.

While knee OA clinical guidelines recommend weight loss [14, 15], they do not specify how best to do this or which dietary approach to use. There is evidence to show that very low calorie diets (VLCDs) involving meal replacements are more effective for inducing significant weight loss and improving physical function than diets that involve lifestyle counselling alone in people with knee OA [29]. Ketogenic VLCDs, whereby carbohydrate intake is additionally restricted (< 50-60 g per day), have also been demonstrated to be an effective and safe means of achieving rapid weight loss in the adult population with overweight and obesity [30] and lead to greater weight loss than low-fat diets in the short-term [31]. An advantage of a ketogenic diet is possible reduction in hunger [32, 33], a feature that may assist with adherence to caloric restriction. The predicted rapid weight loss of 1.5–2.5 kg per week [31] means that those adhering to a ketogenic VLCD frequently achieve a 10–15% weight loss target weight within 12 weeks, an amount likely to have symptomatic benefits for people with knee OA [13].

In a recent randomized controlled trial (RCT), we tested the effectiveness of a telehealth program comprising a ketogenic VLCD delivered by dietitians and exercise delivered by physiotherapists for people with knee OA. The trial showed that this combined program led to greater improvements in pain and function, as well as greater weight loss, when compared to an exercise-only program and to online education control [34]. In our qualitative research, participants described positive experiences with the ketogenic VLCD program, valuing its simplicity and effectiveness [35]. Support from dietitians and a comprehensive suite of educational and behaviour change resources, incorporated with an exercise program, were considered crucial for weight loss success. The telehealth delivery mode was valued for its convenience [35, 36], particularly time efficiency and access. The protocolized and nutritionally complete manner of the ketogenic VLCD using meal replacements means that healthcare practitioners without formal nutrition qualifications, such as physiotherapists, may be capable of effectively and safely supporting such a VLCD for some people with knee OA.

This trial aims to evaluate the effectiveness of a 6-month telehealth physiotherapist-delivered ketogenic VLCD added to exercise compared with telehealth physiotherapist-delivered exercise alone in people with knee OA who have overweight/obesity. The primary hypothesis is that the group offered the diet plus exercise program will lose more weight than the group offered an exercise only program at 6 months. The trial will also evaluate effects on secondary outcomes including body mass index, weight circumference, waist-to-hip ratio, knee pain, physical function, global change in knee problem, quality of life, physical activity levels, internalized weight stigma, physical performance and quadriceps muscle strength. Additional measures will assess adherence, adverse events, intervention fidelity and a range of process outcomes.

## Methods

### Study design

The POWER trial is a two-group parallel, superiority RCT based in Melbourne, Australia. The University of Melbourne Human Research Ethics Committee approved the study (HREC 1955042 ref. 2022–13,143–27,079-5) and the University of Melbourne (Victoria, Australia) is the trial sponsor. The study sponsor will not have any role in study design; collection, management, analysis, and interpretation of data; writing of the final report or the decision to submit the report for publication. The trial was prospectively registered with Clinicaltrials.gov (NCT04733053). This protocol was reported according to the Standard Protocol Items: Recommendations for Interventional Trials statement [37] and trial findings will be reported based on the Consolidated Standards of Reporting Trials statement (CONSORT non-pharmacological treatment interventions) [37] and Template for Interventional Description and Replication (TIDier) [38] guidelines. A trial Data Safety and Monitoring Committee was established consisting of a doctor with expertise in weight loss, a dietitian, a biostatistician and a physiotherapist in clinical practice, none of whom are involved in the trial, have any conflicts of interest or will benefit from the results. The committee will receive a study report every 3 months but will not meet unless warranted. The responsibility of the committee will be to provide recommendations to the chief investigator about continuing, modifying or stopping the trial. There is no planned interim analysis or stopping guidelines.

### Participants

We will recruit 88 participants with chronic knee pain, consistent with a clinical diagnosis of knee OA, from the community in Victoria (Australia) via advertisements, print/radio/social media and our volunteer database. Participants will be included if they:i)meet the National Institute for Health and Care Excellence [39] clinical criteria for OA;age ≥ 45 years;report activity-related knee joint pain;report no knee morning stiffness or morning knee stiffness lasting ≤30 minsii)report a history of knee pain ≥3mths;iii)report knee pain on most days of the past month;iv)report a minimum knee pain score during walking over the past week of 4 on an 11-point numeric rating scale (NRS);v)have a body mass index (BMI) > 27 kg/m^2^ [40];vi)are willing to check their blood pressure (by self or pharmacist/general practitioner) if they are using hypertensive medication and feel light-headed or dizzy during the trial;vii)are able to give informed consent and to participate fully in the interventions and assessment procedures.

Participants are excluded if they:i)are aged over 80 years;ii)weigh > 150 kgs (due to the complexity of additional nutritional requirements for individuals above this weight);iii)are unable to speak English;iv)are on a waiting list for/planning knee/hip surgery or bariatric surgery in next 6 months;v)have had previous arthroplasty on the affected knee;vi)report recent knee surgery on affected knee (past 6 months);vii)report inflammatory arthritis (e.g. rheumatoid arthritis);viii)have had weight loss of > 2 kg over the previous 3 months;ix)are already actively trying to lose weight by any of the following:using formulated meal replacements;being a member of a slimming club (such as Weight Watchers);receiving support from another healthcare practitioner;using prescribed weight loss drugs;using structured meal programs (such as ‘Lite n’ Easy’);x)are unwilling to continue current dietary patterns if randomized to the exercise group;xi)are unable to undertake a ketogenic VLCD without close medical supervision because of the following self-reported conditions:i)Type 1 diabetes;ii)Type 2 diabetes requiring medication apart from metformin;iii)warfarin use;iv)stroke or cardiac event in previous 6 months;v)unstable cardiovascular condition;vi)fluid intake restriction;vii)renal (kidney) problems (unless clearance is obtained from general practitioner, including confirmation that the estimated glomerular filtration rate is > 30 mL/min/1.73m^2^);xii)have any neurological condition affecting lower limbs;xiii)have vegan dietary requirements (due to complexity of delivering a nutritionally complete diet within the ketogenic VLCD).

### Procedures overview

The trial phases are summarized in Fig. 1. Volunteers will undergo screening via an online form then over the telephone by a researcher. Additional clearance to participate will be sought from a general practitioner for anyone who indicates that they have renal dysfunction. A detailed verbal description of the trial including the purpose, aims, possible side effects, content of the interventions and trial commitments will be provided by the researcher during the telephone screening process. Volunteers who are eligible following telephone screening will be sent the Plain Language Statement and Consent Form via email or post by the trial coordinator and will be encouraged to phone the researchers if they have any questions or concerns regarding their contents. After obtaining their written informed consent, either online (REDCap™) or on paper, participants will undergo assessment at the University, including confirmation of weight and BMI eligibility, and complete baseline questionnaires either online (REDCap™) or on paper. A secure data collection platform (Qualtrics or REDCap™) accessible only by password to the researchers will store screening information, trial consent forms and all outcome data. For participants with bilaterally eligible knees, the most symptomatic knee will be deemed the trial knee with respect to outcome measurement. If both knees are equally symptomatic, then the right knee will be chosen. Efforts will be taken to minimize loss of data, including collection of self-reported primary outcome data over the telephone in cases where participants are unable to attend the in person follow up assessment at 6-months.

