### Randomization, blinding and allocation concealment

Eligible participants will be randomised to receive either i) exercise alone or ii) diet plus exercise. The randomization schedule will be computer-generated and prepared by an independent biostatistician. The first list will randomly allocate participants to a physiotherapist (no strata). The second list will randomly allocate participants to an intervention group using variable permuted block sizes and a randomization ratio of 1:1, stratified by physiotherapist and participant sex (due to sex differences in weight gain, weight loss, and attitudes to weight loss [41, 42]). If a physiotherapist is unavailable (e.g. sick, on holiday) participants will be re-randomized to another available physiotherapist using a third list with variable permuted block sizes and stratified by group allocation and sex. The randomization schedule will be stored on a password-protected website (REDCap™) at the University of Melbourne and maintained by a researcher not involved in either participant recruitment or administration of primary/secondary outcome measures. Group allocation is revealed by this same researcher after completion of baseline assessment.

The components of each intervention will be disclosed to participants prior to enrolment as we wish to test the interventions under real world conditions whereby consumers are fully informed about their treatment components before choosing whether they wish to participate. The research staff member collecting non self-reported outcome measures (including the primary outcome) at 6 months will be blinded to group allocation and will be a different person from the one collecting baseline data. This is necessary given that obvious weight loss has the potential to unblind the assessor if baseline and 6 month measures were to be collected by the same person. It is not possible to blind physiotherapists as they are providing interventions to participants in both trial arms to ensure physiotherapist-related factors such as personality or clinical experience are similar between groups and cannot confound results. The statistical analysis plan will be written and published while the biostatisticians are blinded.

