### Outcome measures

Body weight will be measured at baseline and 6 months on the same set of calibrated digital high capacity scales (Seca 813). Weight will be reported in kgs to two decimal places. Change in body weight, expressed as a percentage, is the primary outcome.

There are a number of secondary outcomes. These are measured at baseline and 6 months, unless otherwise stated, and include:i)BMI in kg/m^2^;ii)Waist circumference at mid-abdomen level at its smallest circumference in cm;iii)Waist-to-hip ratio by dividing the waist circumference by the hip circumference at its widest part;iv)Self-reported average knee pain on walking in the last week measured using an 11-point NRS with terminal indicators of ‘no pain’ = ‘0’ and ‘worst pain possible’=‘10’ [49];v)Intermittent and constant osteoarthritis pain measure (iCOAP) [50] with 11 items using a 4-point Likert scale and subscales for constant pain (scored 0 to 20) and intermittent pain (scored 0 to 24). Higher scores indicate higher levels of pain;vi)Physical function subscale of the Western Ontario and McMaster Universities Osteoarthritis Index (WOMAC) [51] scored over 17 items, using a 4-point Likert scale with a total score between 0 and 68. Higher scores indicate more severe dysfunction;vii)Perceived global change in knee problems scored on a 7-point Likert scale from ‘much worse’ to ‘much better’ [52] at the 6-month time point only. Participants who indicate that they are “moderately better” or “much better” will be categorized as ‘improved’. All other respondents will be categorized as ‘not improved’;viii)Health-related quality of life using the Assessment of Quality of Life (AQoL) (version AQoL-6D) [53], a 20-item instrument with scores ranging between − 0.04 to 1.0 and higher scores indicating higher quality of life;ix)Physical activity levels evaluated using the physical activity scale for the elderly (PASE) [54] with scores from 0 to 400 with higher scores indicating greater levels of physical activity;x)Weight Self-Stigma Questionnaire (WSSQ) to evaluate internalized weight stigma [55] reported via two subscales (self-devaluation and fear of enacted stigma) and a combined total of 0–60 with higher scores indicating greater internalized weight stigma;xi)Physical performance measures recommended by the Osteoarthritis Research Society International [56] and assessed by a researcher blinded to group allocation;30s chair sit-to-stand test: The number of complete chair stands achieved in 30s will be reported [56]. Higher scores indicate better physical function.40 m fast-paced walk test: The total time taken to walk 40 m quickly but safely will be recorded, and reported in speed (m/s) [56]. Faster walking speeds indicate better physical function.6-step stair climb test: The total time taken to ascend and descend a flight of six stairs will be recorded [57]. Use of the handrail is optional. Shorter completion times indicate better physical function.xii)Maximum voluntary isometric strength of the knee extensors measured on an isokinetic dynamometer (HUMAC, CSI, Boston) with the knee held at 60 degrees flexion. The maximum torque reached over 3 repetitions of 5 seconds, normalized to body mass, will be recorded in Nm/kg.

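### Self-reported telephone weights are allowed as primary outcome data, in conflict with the blinded, same-scale definition of that outcome, and their status in the analysis is not fixed

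*Protocol article*

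**What the plan says.** Four places in the protocol article bear on this.

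- **Abstract, Methods:** "The primary outcome is percentage change in body weight measured by a blinded assessor".
- **Randomization, blinding and allocation concealment:** "The research staff member collecting non self-reported outcome measures (including the primary outcome) at 6 months will be blinded to group allocation". The primary outcome is thus placed among the measures that are not self-reported. The same section says that participants are told the content of both interventions before they enrol.
- **Outcome measures:** "Body weight will be measured at baseline and 6 months on the same set of calibrated digital high capacity scales". It adds: "Weight will be reported in kgs to two decimal places".
- **Procedures overview:** the fallback for people who miss the 6-month visit is "collection of self-reported primary outcome data over the telephone in cases where participants are unable to attend". The section offers this as one of its steps against data loss.

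The Data analysis plan section compares mean percentage change in weight by linear regression, adjusted for baseline weight, sex and physiotherapist. It calls for multiple imputation when more than 5% of primary outcome data are missing. It does not say whether a telephone weight is observed or missing.

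**The concern.** A weight given over the telephone is not measured by an assessor and is not taken on the trial scales. It comes from someone who can recognise their own treatment. Procedures overview nevertheless calls it primary outcome data and presents it as a way to limit data loss, so the natural reading is that it enters the analysis as an observed value.

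Three things follow on that reading.

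1. For these participants, percentage change compares a clinic-scale baseline with a follow-up weight from a home scale or from memory.
2. Reporting error could differ between arms. Only the diet plus exercise group sets a weight-loss goal with the physiotherapist and is encouraged to track weight weekly. That could make its reports more accurate, or more favourable, than those of the exercise group.
3. Each telephone weight counted as observed lowers the missing proportion, and that proportion decides whether multiple imputation is used. A self-reported value can therefore influence which primary analysis is run.

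**Working it through.** **The plan's own figures (Trial sample size).** Difference 5 points, SD 7.5, two-sided alpha 0.05, power 0.80. The two-sample t-test needs 36.3, so 37 per group. Dividing by 0.85 gives 43.5, so 44 per group and 88 in total. Both stated figures reproduce.

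**Standard error of the group difference.** SE = SD × √(2/n).
- n = 37 (15% lost): 7.5 × √(2/37) = 1.74.
- n = 44 (every telephone weight counted, nobody lost): 7.5 × √(2/44) = 1.60.

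**Bias in the group difference.** Let p be the share measured by telephone, taken as equal in the arms. Let d be the difference between arms in mean reporting error (kg) and W the mean baseline weight (kg). Then bias in percentage points = 100 × p × d / W. The document gives none of the three; all are assumed.

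| p | d (kg) | W (kg) | Bias (points) | Share of 5-point target | Bias / SE (1.60) |
|---|---|---|---|---|---|
| 0.05 | 1 | 110 | 0.05 | 1% | 0.03 |
| 0.10 | 2 | 95 | 0.21 | 4% | 0.13 |
| 0.15 | 4 | 85 | 0.71 | 14% | 0.44 |

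The last row needs all three extremes at once. Under a true null, two-sided type I error = 1 − Φ(1.96 − bias/SE) + Φ(−1.96 − bias/SE). With SE 1.60 this is 0.050, 0.052 and 0.073 for the three rows. On a narrower assumption (share up to 15%, differential error of 1 to 3 percentage points of body weight) the bias is 0.05 to 0.45 points and the type I error at most about 0.059.

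**Direction.** With unequal shares p₁, p₂ and errors e₁, e₂ in points of body weight, bias = p₁e₁ − p₂e₂.
- Shares 15% and 5%, errors 2 and 1: 0.30 − 0.05 = +0.25.
- Shares 5% and 15%, errors 1 and 1: 0.05 − 0.15 = −0.10.
- Equal shares and equal errors: 0.

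The sign depends on quantities that the document does not give.

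**Responder proportions.** For one person at 95 kg, 2 kg of under-reporting is 100 × 2/95 = 2.1 points. A true loss of 3.5% would be recorded as 5.6% and would cross the 5% threshold.

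**Imputation trigger.** 4/88 = 4.5% and 5/88 = 5.7%, so the trigger needs 5 or more missing. The planned 15% loss is 0.15 × 88 = 13.2, about 13 people. If 9 of 13 non-attenders gave telephone weights and these counted as observed, 4 would be missing and imputation would not be triggered. If they counted as missing, 13/88 = 14.8% and it would be.

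**Cost of treating them as missing.** 44 × 0.85 = 37.4, about 37 per group, with t-test power of about 0.81 for the 5-point difference.

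**The case against.** The strongest defence is that Procedures overview describes data collection, not analysis. No sentence puts telephone weights into the primary regression or counts them as observed under the 5% rule. A full statistical analysis plan is promised, written while the statisticians are blinded, and classifying fallback measurements is commonly left to such a plan. This stands in part: a reader might infer that the primary comparison definitely mixes the two kinds of measurement, and the article does not say so. But a later plan would not remove the conflict between the sections of this article, and the words used for the telephone data point towards observed values.

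Four stronger readings are tempting and are not supported.

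- Weight is not the only endpoint protected by blinding. The abstract lists BMI, waist measures, physical performance and quadriceps strength as blinded too.
- No single section defines the outcome as both blinded and same-scale. The abstract and the blinding section give the first element; Outcome measures gives the second.
- The imputation rule is not necessarily switched off. That happens only if telephone weights count as observed and bring missingness down to 5% or below.
- The bias does not necessarily favour the diet arm. Regular weighing may make that arm's reports more accurate, and larger under-reporting in the exercise arm would shrink the difference.

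It is also fair to say that collecting these weights is sensible. If non-attenders lost less weight than attenders, a telephone weight carries information that would otherwise be lost. That argues for keeping the values, not for treating them as equivalent to clinic measurements.

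**Conclusion.** The inconsistency is certain. The article allows self-report for an outcome that it elsewhere describes as blinded, not self-reported and measured on the same scales throughout. That telephone weights count as observed is the natural reading but is not stated outright.

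The effect on the mean difference is probably modest: about 0.05 to 0.7 points on assumed inputs, of unknown direction, and zero if shares and errors match between arms. It is unlikely by itself to overturn a 5-point effect. The proportions reaching 5% and 10% loss are more sensitive for individuals, and the choice to impute can turn on a handful of values. The case for acting rests as much on the accuracy of the blinded-measurement claim, and on fixing the rule before results are known, as on the size of the bias.

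**What to change.** Reconcile the sections by stating that the primary outcome is assessor-measured weight on the trial scales. Then:

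1. Treat telephone weights as missing in the primary analysis and when applying the 5% trigger.
2. Include them as an auxiliary variable in the multiple imputation, so that their information is kept.
3. Report an analysis that counts them as observed as a sensitivity analysis.

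If the investigators prefer to keep them as observed, they should correct the wording on blinded assessment and on the outcome not being self-reported, and add a sensitivity analysis using measured weights only, with multiple imputation.

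In either case, record how each 6-month weight was obtained and report the number of telephone weights by arm.

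The cost is wording in the protocol and analysis plan and slightly less precision. That loss lies within the existing 15% allowance (about 37 per group, power about 0.81), so no extra participants are needed. No new data collection is needed either. A new questionnaire item for everyone would probably come too late for early participants, since recruitment began in October 2021.
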